### 2.3. Sample Size Calculation

The present study is not powered for any confirmatory inference. The targeted roster sizes (approximately 15–25 athletes per team) are sufficient to evaluate feasibility and engagement and to provide preliminary clustering estimates (i.e., intraclass correlation coefficient). We will report these estimates with 95% confidence intervals. Precision will be limited by the small number of teams. Published intraclass correlation coefficient (ICC) values will also inform power for a future cluster-randomized trial.

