If more than 50% of parents or guardians on a selected team decline participation, that team will be replaced by another eligible team from the same school, which will inherit the school’s randomized condition to preserve the integrity of the cluster randomization. No re-randomization will occur at the team level. Parents or guardians of student-athletes in the waitlist control condition will receive similar study information but will be informed that their child(ren) will complete online surveys across the season and gain access to the TN mobile application after the season ends.

For the intervention group, a 30 min online pre-season training will be offered to orient participants to TN, including installation, initial setup, and core functions. Both the intervention and control groups will complete online surveys at three time points: the beginning of the season (baseline), mid-season, and the end of the season. Before each survey, participants will be reminded that their participation is voluntary, that they may withdraw at any time without penalty, and that their responses will be anonymous and not shared with coaches, parents, or school staff.

All survey data will be de-identified and stored on encrypted servers, accessible only to the research team. Coaches will not have access to individual student responses, only to aggregated, anonymized team-level summaries where appropriate. Neither personal-level data will be visible to schools nor to the TN developers.

Within two weeks of the postseason, coaches and student-athletes in the control group will be introduced to TN through a short tutorial and guided installation instructions via email. The study protocol and all related materials will be reviewed and approved by the Institutional Review Board prior to participant recruitment. All procedures will be conducted in accordance with the ethical principles outlined in the Declaration of Helsinki.

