### 2.8. Measures

Demographic characteristics and student-athlete outcomes will be measured using online surveys at the beginning, middle, and end of the season. Demographic characteristics include the ages, genders, races/ethnicities, and types of sports of coaches and student-athletes. Student-athletes will be asked to self-report their physical activity (over the past 7 days): “On how many days were you physically active for a total of at least 60 min per day? (Add up all the time you spent in any kind of physical activity that increases your heart rate or makes you breathe hard some of the time.)”

In addition, student-athletes will be asked to self-report four brief mental-health–related items adapted from validated adolescent screening tools. Items include the following:(1)“When you feel sad or hopeless, are there adults that you can turn to for help?” ([Bibr B2-behavsci-16-00268]);(2)“During the past two weeks, how often have you been bothered by feeling nervous, anxious, or on edge?” ([Bibr B19-behavsci-16-00268]);(3)“During the past two weeks, how often have you been bothered by not being able to stop or control worrying?” ([Bibr B19-behavsci-16-00268]);(4)“During the past 12 months, did you ever feel so sad or hopeless almost every day for two weeks or more in a row that you stopped doing some usual activities?” ([Bibr B2-behavsci-16-00268]).

These items are used descriptively to complement standardized scales and provide context for student-athlete well-being ([Bibr B2-behavsci-16-00268]; [Bibr B19-behavsci-16-00268]).

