### 2.9. Data Analysis

Analyses will use linear mixed-effects models (LMMs) estimated via REML to account for nesting (student-athletes within teams within schools) and to accommodate unbalanced repeated measures. Fixed effects will include condition (intervention vs. waitlist control), time (baseline, mid-, and end-season), and their interaction; random intercepts will be specified for team and school. Missing data will be handled by maximum-likelihood under MAR; if attrition exceeds 20%, multiple imputation will be used as a sensitivity analysis. Prespecified covariates include type of sport, gender, grade, and prior mental-health support. Given the pilot nature and very limited clusters, results will emphasize descriptive effect sizes with 95% CIs and ICCs/design effects rather than confirmatory *p*-values; where *p*-values are reported, we will control the false discovery rate (Benjamini–Hochberg) across outcomes.

Because cluster-randomized designs with few clusters are susceptible to chance baseline imbalances, baseline values of each outcome will be included as covariates in all longitudinal models. This baseline-adjusted specification is expected to improve precision and reduce bias attributable to baseline differences between conditions. As a sensitivity analysis, estimates will be examined with and without adjustment for multiple comparisons to evaluate the robustness of observed patterns. These analyses are intended to support transparent interpretation of exploratory findings.

Verbatim transcriptions of coach and student-athlete interviews will be analyzed using rapid content analysis to identify key usability insights, perceived benefits, and improvement opportunities related to the TN platform. The analysis will prioritize efficiency and practical relevance in studies with small samples, maintaining analytic rigor through structured coding and documentation. Two researchers will independently review transcripts, generate preliminary codes, and summarize key points within a shared matrix. Codes will then be grouped into higher-order categories to capture salient patterns in user experience and acceptability ([Bibr B6-behavsci-16-00268]). Findings will be summarized thematically but interpreted as exploratory, descriptive feedback rather than claims of thematic saturation. NVivo 12 ([Bibr B31-behavsci-16-00268]) will be used for data organization and coding.

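### Maximum likelihood under MAR does not cover a missing baseline score once baseline is a covariate, and an attrition trigger would not count the athletes lost this way

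*Protocol article*

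**What the plan says.** All of the statistical wording is in section 2.9 of the protocol article.

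- Model: "Analyses will use linear mixed-effects models (LMMs) estimated via REML to account for nesting".
- Time factor: its levels are given as "time (baseline, mid-, and end-season), and their interaction" with condition, so the baseline score is one of the outcome values.
- Baseline adjustment: "baseline values of each outcome will be included as covariates in all longitudinal models", so the baseline score is also a predictor.
- Other predictors: "Prespecified covariates include type of sport, gender, grade, and prior mental-health support".
- Missing data: "Missing data will be handled by maximum-likelihood under MAR; if attrition exceeds 20%, multiple imputation will be used as a sensitivity analysis".

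The article does not define attrition and gives no separate rule for a missing baseline score or covariate.

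On data collection, section 2.8 says "Demographic characteristics and student-athlete outcomes will be measured using online surveys at the beginning, middle, and end of the season", and section 2.4 adds "Before each survey, participants will be reminded that their participation is voluntary". A skipped baseline survey, or a skipped scale within it, is therefore possible. Section 2.3 gives the size: "The targeted roster sizes (approximately 15–25 athletes per team", in four teams.

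**The concern.** The missing-data sentence reads as if likelihood estimation takes care of all missing values. That holds for missing outcomes. It does not hold for predictors, and the baseline-adjustment sentence turns one of the three outcome measurements into a predictor.

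If the section is followed as written, an athlete who misses the baseline survey but completes the other two contributes nothing to the adjusted model. The fallback does not catch this. It depends on attrition, and this athlete has not been lost to follow-up. Even when triggered, multiple imputation is only a sensitivity analysis, so the main estimates still omit the athlete.

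The study is exploratory, so no confirmatory test is at stake. The outputs at stake are the effect sizes with confidence intervals and the ICCs and design effects, which section 4 says will guide the sample size of a full trial. If athletes who skip the baseline survey differ from the others, those outputs describe a selected subset.

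**Working it through.** The plan states no figure that depends on missing data, so there is none to reproduce. The check has four steps.

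**1. What the stated likelihood covers.** A REML mixed model uses the distribution of the outcome given the fixed-effect predictors. A row with a missing outcome is skipped, and the athlete's other rows remain. A row with a missing predictor has no computable mean and contributes nothing. An athlete's baseline score takes the same value in every one of that athlete's rows, so if it is missing all the rows go. This happens outcome by outcome. A likelihood that also modelled the predictors would avoid it, but section 2.9 names no such model.

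**2. Demonstration.** A REML mixed model, simplified to a team random intercept, was fitted to 80 simulated athletes at three waves. By construction 8 athletes had no baseline score, 8 others had no answer on one covariate, and nobody was lost to follow-up.

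| Model | Athletes used | Outcome rows used |
|---|---|---|
| Condition × time only | 80 | 232 of 232 observed |
| Plus baseline score and covariates | 64 | 192 of 232 observed |

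The 40 observed rows lost are 8 × 2 = 16 from athletes without baseline and 8 × 3 = 24 from athletes without the covariate. The 20% loss of athletes was built in. The demonstration shows the mechanism at zero attrition, not its likely size.

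**3. Athletes affected.** Rosters: 4 × 15 = 60 to 4 × 25 = 100. The article gives no missingness rate, so the share without a baseline score is an assumption.

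| Assumed share without baseline | Of 60 | Of 100 |
|---|---|---|
| 5% | 3 | 5 |
| 10% | 6 | 10 |
| 20% | 12 | 20 |

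Each row is compatible with 0% attrition.

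**4. Precision.** Athletes are clustered, so the relevant quantity is the variance of a team mean, proportional to ICC + (1 − ICC)/m for m athletes per team. Take m = 20, the middle of the stated range, and assume a team ICC of 0.05 or 0.10.

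- ICC 0.05: m = 20 gives 0.05 + 0.95/20 = 0.0975; m = 18 gives 0.1028; m = 16 gives 0.1094. SE ratios: √(0.1028/0.0975) = 1.027 and √(0.1094/0.0975) = 1.059.
- ICC 0.10: m = 20 gives 0.10 + 0.90/20 = 0.1450; m = 18 gives 0.1500; m = 16 gives 0.1563. SE ratios: √(0.1500/0.1450) = 1.017 and √(0.1563/0.1450) = 1.038.

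Losing 10–20% of athletes therefore raises the SE of a team mean by about 2–6%. Variation between schools is unaffected by athlete numbers and would dilute this further in the comparison of conditions.

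**The case against.** The strongest reply is that this is silence, not error. The article never prescribes complete-case deletion, attrition is undefined, and an analysis plan that is not shown could settle both. That would stand if the article had said nothing. It does not, because the article states a missing-data rule and a model, and under that model the rule does not reach a missing baseline score. The point about attrition does rest on the word's ordinary meaning.

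Several stronger readings are tempting, and the documents do not support them.

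- *Late joiners are dropped.* A reader might infer such a group, but nothing in the article provides for enrolment after baseline.
- *Athletes unwilling to disclose mental-health support are dropped.* Section 2.8 does not list grade or prior support among the survey items, and its four mental-health items do not ask about prior support. The article does not say how either covariate is obtained.
- *Covariates add heavily to the loss.* Sport type is known from the team. Demographics are asked at three waves, so a value missed once can be recovered. Only a covariate never obtained excludes an athlete.
- *A fifth to a third of athletes are lost.* If baseline score, gender, grade and prior support are each missing in 5% or 10%, independence gives 1 − 0.95⁴ = 18.5% or 1 − 0.90⁴ = 34.4%. Both the rates and the independence are assumptions. A missed baseline survey would remove several items together, and with full overlap the loss is 5% or 10%.
- *Standard errors rise 5–12%.* That is 1/√0.9 = 1.054 and 1/√0.8 = 1.118, which treats athletes as independent.

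It is also fair that the study is exploratory and unpowered (sections 2.3 and 3), and that section 4 lists data completeness as a feasibility metric, so missingness should be visible in the report. This limits the weight of the point. It does not bring excluded athletes back into the estimates.

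**Conclusion.** The point holds for missing baseline scores and for covariates never obtained at any wave. Under the REML model of section 2.9, with baseline as a covariate, such athletes leave the model for that outcome whatever they report later. A trigger based on loss to follow-up does not count them.

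The size cannot be fixed from the documents. At an assumed 5–20% without a baseline score, 3–20 of 60–100 athletes are excluded per outcome. For assumed ICCs of 0.05–0.10 and 20 athletes per team, a 10–20% loss costs about 2–6% on the SE of a team mean. The main concern is selection in the effect sizes and ICCs passed on to the next trial. The direction of any bias is unknown.

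A reader might infer that the plan orders a complete-case analysis or that a large share of the sample will be lost. Neither is shown. This is a moderate point, worth correcting because the correction is cheap.

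**What to change.** In section 2.9:

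1. Choose one role for baseline.
   - Either keep it only as a level of the outcome and remove the baseline-as-covariate sentence. The likelihood then covers a missing baseline, and baseline differences are handled through the condition-by-time contrasts. This needs a term linking an athlete's own repeated measures; the section names random intercepts for team and school only.
   - Or keep it as a covariate, remove baseline from the outcome levels, and state how missing baseline scores are imputed in the main analysis. Filling in the overall mean with a missingness indicator is a weaker choice here. Its usual justification is covariate balance from randomization, and each condition has one school.
2. State that any covariate still missing after all three waves is imputed.
3. Base the 20% trigger on all athletes the model would exclude for any reason, and report that number per outcome and condition.

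The cost is a few sentences and a small amount of extra analysis work. No new data are needed.

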### 2.4. Procedure

Coaches and high school student-athletes will be recruited from a purposive sample of two public high schools within a district that reflects a diverse demographic composition. Schools will serve as the unit of randomization and will be randomly assigned to either the TN intervention group or the waitlist control group. Four weeks prior to the start of the season, head coaches will be contacted via email, using the contact information provided by the district athletic director. Following pre-screening to confirm their coaching role, coaches will be invited to complete an online enrollment survey that includes the purpose of the study, its procedures, and an option to opt out. Coaches who consent to participate will be listed under the intervention or control condition. Two teams from each school will then be randomly selected for inclusion, resulting in a total of four participating teams. To prevent potential contamination, both teams from the same school will remain in the same condition, consistent with school-level group assignment. Teams in the intervention group will have access to TN throughout the season, whereas teams in the control group will serve as a waitlist control and receive access after the study is completed.

Parental consent and student-athlete assent will follow IRB-approved procedures appropriate for research with minors. Given that the study involves a non-clinical, educational mobile platform and poses no greater than minimal risk, the research team will seek for a passive (opt-out) parental consent process, consistent with school district research policies.

Parents or legal guardians will receive an informational letter via email two weeks before data collection, describing the study purpose, procedures, confidentiality protections, and voluntary nature of participation. The letter will include both an online opt-out form and contact information for the research team. Those who do not opt out will be considered to have provided consent. Student-athletes will then provide electronic assents prior to participation, with the option to withdraw at any time without penalty.

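### Type of sport, fitted as a covariate over four unmatched teams, will probably alias the condition main effect or leave it no team-level degrees of freedom; two other named covariates have no listed measure

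*Protocol article*

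**What the plan says.** Section 2.9 (Data Analysis) sets out a linear mixed model fitted by REML. On the fixed part: "Fixed effects will include condition (intervention vs. waitlist control), time (baseline, mid-, and end-season), and their interaction". On the random part: "random intercepts will be specified for team and school". It then adds: "Prespecified covariates include type of sport, gender, grade, and prior mental-health support". The baseline value of each outcome is a further covariate in every longitudinal model.

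Section 2.4 (Procedure) fixes the clusters: "Schools will serve as the unit of randomization and will be randomly assigned to either the TN intervention group or the waitlist control group". On teams: "Two teams from each school will then be randomly selected for inclusion, resulting in a total of four participating teams". It also states that "both teams from the same school will remain in the same condition, consistent with school-level group assignment". No matching or stratification by sport is described. A team with more than half of parents declining is replaced by another eligible team from the same school, again with no condition on sport.

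Section 2.8 (Measures) says: "Demographic characteristics include the ages, genders, races/ethnicities, and types of sports of coaches and student-athletes". It adds one physical-activity item, four brief mental-health items that are to be used descriptively, and the scales in 2.8.1 to 2.8.6.

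Sections 2.3, 2.9 and 4 make ICCs a main product of the pilot, and Sections 2.9 and 4 add design effects. They are to guide planning of a larger cluster-randomized trial.

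**The concern.** A covariate that is constant within a team can only be estimated from differences between teams, and there are four. Condition is also constant within a team, so sport and condition compete for the same four team means. With as many sport levels as teams, nothing is left for condition. With three levels arranged across the schools, condition is estimable but nothing is left over to estimate team-to-team variation.

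Two things are at stake. One is the condition main effect. It matters most if the model is fitted to mid- and end-season scores with baseline as a covariate, because that term then carries the treatment contrast. The other is the team variance. A model whose fixed effects reproduce every team mean cannot inform it, yet the next trial's planning depends on it.

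A smaller matter is that two of the four named covariates do not appear among the measures that the article lists.

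**Working it through.** The article gives no power, alpha or sample-size figure on this point, so there is nothing of its own to reproduce. The check is of the design matrix and the team draw.

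**Inputs.** Two schools, one per arm, and two teams per school, so four teams (Section 2.4). Fixed effects: condition, time with three levels, their interaction, baseline, type of sport, gender, grade and prior support (Section 2.9). Rosters are 15 to 25 (Section 2.3); 20 per team was used, and the rank result does not depend on it. Assumed, not in the documents: one model level per sport, one team per sport, and K sports offered at both schools.

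**Four different sports (A, B in the intervention school; C, D in the control school).** Columns: intercept 1 + condition 1 + time 2 + condition-by-time 2 + baseline 1 + gender 1 + grade 1 + prior support 1 + sport 3 = 13. The rank is 12. The dependency is visible directly: with A as reference, the condition indicator equals 1 minus the C dummy minus the D dummy. The condition main effect is not estimable.

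**One sport shared (A, B against A, C).** Team-level columns: intercept, condition, B, C = 4, for 4 teams. Residual df = 4 − 4 = 0. The B and C teams are each absorbed by their own dummy, so condition rests on the two A teams, one against one.

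**Same two sports at both schools (A, B against A, B).** Team-level columns: intercept, condition, one sport dummy = 3. Residual df = 4 − 3 = 1.

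**No sport term.** Team-level columns: intercept and condition = 2. Residual df = 4 − 2 = 2. At school level it is 2 − 2 = 0, with or without sport.

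**Interaction.** In every sport pattern, the condition-by-time contrasts remain estimable when sport enters only as a main effect. They are lost in the aliased patterns only if a sport-by-time term is added, which Section 2.9 does not plan.

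**Team variance.** In the first two patterns the intercept, condition and sport columns span all four team indicators. REML works on contrasts free of the fixed effects, so the team intercepts cancel from every such contrast and the likelihood is flat in the team variance.

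**Chance of each pattern.** Fix the pair drawn at one school. The other school has C(K,2) possible pairs: C(K−2,2) share no sport, 2(K−2) share one, and 1 shares both.

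| K | no sport shared (aliased) | one shared (0 df) | both shared (1 df) |
|---|---|---|---|
| 4 | 1/6 = 17% | 4/6 = 67% | 1/6 = 17% |
| 6 | 6/15 = 40% | 8/15 = 53% | 1/15 = 7% |
| 10 | 28/45 = 62% | 16/45 = 36% | 1/45 = 2% |
| 20 | 153/190 = 81% | 36/190 = 19% | 1/190 = 0.5% |

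Aliased or saturated together: 5/6 = 83% at K=4, rising to 189/190 = 99% at K=20.

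**Covariates against measures.** Type of sport and gender in 2.9 both appear in the 2.8 list. Grade does not; age is the nearest variable. Prior mental-health support does not; the nearest item asks whether there are adults to turn to now, which is not support received in the past.

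**The case against.** The strongest reply is that the research questions in Section 1 mostly ask about change over the season between arms. That is the condition-by-time interaction, which survives. This stands. A reader might infer that the planned model cannot estimate any treatment effect; the documents do not support that. What is exposed is the condition main effect and the team variance. Because Section 2.9 both lists baseline as a time level and enters it as a covariate, a fit to post-baseline scores alone is possible, and there the main effect matters directly.

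Second, the percentages depend on K and on one level per sport, and the article fixes neither. A coarse coding, such as two broad types, would use 1 df and alias condition only if type split exactly by school. This stands as a limit on the size, but no coarse coding is stated.

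Third, condition is already confounded with school, and Section 3 concedes that inference from two clusters is fragile. True, and removing sport does not cure it. The concession does not cover the loss of the remaining team-level information through a covariate.

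Fourth, an ICC could come from a model without sport. It could, but Section 2.9 does not set one apart.

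A reader might also infer that grade and prior support will be missing for everyone. That is not shown: the demographic list is introduced as what is included, and the instrument appendix is not at hand. Nor do the documents say whether squads are single-sex, so gender cannot be claimed to share the problem.

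**Conclusion.** The point holds for the condition main effect and for the team-level ICC and design effect from the adjusted model. With sport coded one level per sport and no matching, about 83% to 99% of draws (K from 4 to 20, assuming common sport lists and one team per sport) leave the main effect aliased or the team level saturated. It does not extend to the condition-by-time contrasts under the planned model, and it is separate from the school confounding, which stays at 0 school-level df throughout.

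On grade and prior mental-health support, the supportable statement is that Section 2.9 names them and Section 2.8 lists no measure for them. That is a matter of reconciliation.

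**What to change.** Remove type of sport from the fixed effects in Section 2.9 and report it descriptively by team. This restores 2 team-level df. It costs nothing to implement; the downside is no model adjustment for sport.

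Optionally, select the same two sports at both schools and keep sport only as the 1-df matching factor. The replacement rule in Section 2.4 would then have to require the same sport, or a single replacement could break the match. The cost is that sports offered at only one school are excluded, and 1 team-level df is left instead of 2.

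Reconcile Sections 2.8 and 2.9: add items for grade and prior mental-health support to the baseline survey, or delete those covariates. Age is already collected and can stand in for grade. The cost is at most two survey items, but they must be in place before baseline.

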## 2. Materials and Methods

### 2.1. Setting and Design

This study will be conducted in collaboration with two high schools in North America, with data collected from two interscholastic teams at each high school. Two selected high schools will be randomly assigned to either the intervention group, which will use TN, or to a waitlist control group, which will not receive the intervention during the study period. Both groups will follow the rules set by their state’s interscholastic governing body and have access to standard school resources. Coaches will be recruited and informed consent will be obtained prior to student-athlete recruitment. Then, their athletes will be recruited accordingly. Informed consent will be obtained from parents or legal guardians before student-athlete recruitment, and assent will be obtained from all student-athletes. The interventional effect will be evaluated using a quasi-experimental design, and student-athlete outcomes will be measured at the beginning, midpoint, and end of the sport season. To gain an understanding of the experience of using TN, a subgroup of coaches and student-athletes will be recruited for interviews with open-ended questions. Altogether, we will analyze the qualitative and quantitative data using statistical and thematic analyses accordingly. While no monetary incentives will be provided, coaches and student-athletes will be invited to a brief end-of-season presentation where the research team will share key findings and practical takeaways. Participants will also receive a printed brochure with evidence-informed, actionable strategies and resources on mental health and team well-being. This protocol has been preregistered on the Open Science Framework (Registration DOI: 10.17605/OSF.IO/85S9G).

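### Baseline enters the same model as an outcome occasion and as a covariate, so the condition-by-time estimate receives no baseline adjustment

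*Protocol article*

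**What the plan says.** Section 2.1 sets three measurement occasions: "student-athlete outcomes will be measured at the beginning, midpoint, and end of the sport season". Section 2.9 then defines one linear mixed model for the outcomes: "Fixed effects will include condition (intervention vs. waitlist control), time (baseline, mid-, and end-season), and their interaction". For clustering, "random intercepts will be specified for team and school"; no athlete intercept is listed. The next paragraph of 2.9 adds that "baseline values of each outcome will be included as covariates in all longitudinal models", because few clusters make chance imbalance likely, and gives the expected benefit: "This baseline-adjusted specification is expected to improve precision and reduce bias attributable to baseline differences between conditions".

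Nothing in 2.9 takes baseline out of the response once it is a covariate, lets the covariate interact with time, or constrains the arms to a common baseline mean. The section does not say whether the condition-by-time term or the adjusted arm difference at a given time will be reported.

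**The concern.** The baseline score is an outcome row and also a predictor of every row, including itself. Two things follow. First, the term that most directly answers the questions about change over the season (RQ1 to RQ3 in section 1) cannot be affected by the covariate when data are complete, although 2.9 credits the covariate with less bias and better precision. Second, one row in three is predicted partly from itself, which distorts the baseline slope and the pooled residual variance behind any adjusted arm difference.

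The study plans to emphasise effect sizes with 95% confidence intervals over p-values, so the estimate and its interval are the main product. A reader would take the reported contrast to be baseline-adjusted when it is a plain difference in change. The rule covers every longitudinal model, so every outcome is affected.

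**Working it through.** The plan gives no SD, correlation or effect size, so there is no figure of its own to reproduce. From the documents: three occasions (2.1), four teams (2.2) of "approximately 15–25 athletes per team" (2.3), and the model in 2.9. Assumed: outcome SD 1 at each occasion, the same correlation r between any two occasions of an athlete, and 20 athletes per team, so 40 per arm.

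**1. Cancellation.** Write the fixed part as E(Y_ij) = μ + αC + τ_j + δ_jC + βY_i0, with j = 0, 1, 2 and δ_0 = 0. The end-season change is E(Y_i2) − E(Y_i0) = (τ_2 − τ_0) + δ_2C. The term βY_i0 is in both rows and drops out. With complete data, the estimate of δ_2 is the difference in mean change for any β.

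Numerical check on simulated data (r = 0.5, team SD 0.2, persistent baseline gap 0.5 SD, end-season effect 0.3 SD, all assumed): 0.88447 with the covariate, without it, and as the raw change difference. In 150 further REML fits the largest discrepancy with versus without the covariate was 4e-15. With 10, 20 and 30% random dropout at end-season, the mean absolute departure from the completers' raw change difference was 0.021, 0.031 and 0.040 SD. The averages still agreed (0.301 against 0.298 at 20%).

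**2. Reported SE of that contrast (r = 0.5).** With only team and school intercepts, an athlete's rows are treated as otherwise independent, so SE = √(4σ²/40).
- Without the covariate: σ² = 1, SE = √(4/40) = 0.316.
- With it: slope b = (1 + 2 × 0.5)/3 = 0.667; baseline-row residual variance (1 − 0.667)² = 0.111; follow-up rows 1 + 0.444 − 0.667 = 0.778; pooled (0.111 + 2 × 0.778)/3 = 0.556; SE = √(4 × 0.556/40) = 0.236.
- True SD of the estimate in both cases: √(2 × 2(1 − 0.5)/40) = 0.224.

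The fits averaged 0.314 and 0.234. The SE falls because the covariate stands in for the missing athlete effect; the estimate does not change. In the single data set with an athlete intercept, the SE was 0.21393 with and without the covariate.

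**3. Adjusted arm difference.** The slope pools one self-regression and two follow-up regressions: b = (1 + 2r)/3. Residual variance is (1 − b)² for baseline rows and 1 + b² − 2br for follow-up rows.

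| r | b | Baseline-row SD | Follow-up variance | Pooled variance | Pooled/follow-up SD |
|---|---|---|---|---|---|
| 0.4 | 0.60 | 0.40 | 0.880 | 0.640 | 0.85 |
| 0.6 | 0.73 | 0.27 | 0.658 | 0.462 | 0.84 |
| 0.8 | 0.87 | 0.13 | 0.364 | 0.249 | 0.83 |

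The residual SD is 15–17% too small for the follow-up rows.

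**4. What each contrast returns** (effect 0.3, baseline gap 0.5 SD, r = 0.5).
- Stable gap: raw end-season difference 0.3 + 0.5 = 0.80. Change: 0.80 − 0.50 = 0.30. Stated model, adjusted: 0.80 − 0.667 × 0.5 = 0.47. Follow-up rows only, adjusted: 0.80 − 0.5 × 0.5 = 0.55. Simulated averages: 0.297, 0.461 and 0.542.
- Chance athlete-level gap: raw difference 0.3 + 0.5 × 0.5 = 0.55. Change: 0.55 − 0.50 = 0.05. Stated model, adjusted: 0.55 − 0.333 = 0.22. Follow-up rows only, adjusted: 0.55 − 0.25 = 0.30.

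**5. Precision with a stable school effect of SD s, one school per arm (r = 0.5).** Change: variance 2 × 2(1 − r)/40 = 0.05, SD 0.224 for any s. Follow-up rows only, adjusted: 2(1 − r²)/40 + 2s²(1 − r)² = 0.0375 + 0.5s².

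| s | Change | Adjusted, formula | Adjusted, simulated |
|---|---|---|---|
| 0 | 0.224 | 0.194 | 0.196 |
| 0.1 | 0.224 | 0.206 | 0.207 |
| 0.2 | 0.224 | 0.240 | 0.241 |
| 0.3 | 0.224 | 0.287 | 0.285 |

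A separate check at s = 0.2 gave 0.225 against 0.246. Break-even: 0.5s² = 0.0125, so s = 0.16, a school share of variance of 0.025/1.025 = 2.4%.

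**The case against.** The strongest reply is that an unadjusted difference in change is a valid answer to research questions about patterns of change, and that 2.9 never names the condition-by-time term as the key contrast. Both points stand. They excuse the contrast but not the benefit claimed for the covariate.

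A reader might go further than the documents allow in four ways.
- That no baseline adjustment happens at all. The adjusted arm difference does move: in the stable-gap simulations it averaged 0.461, against about 0.79 with no adjustment.
- That baseline rows have almost no residual. Their residual SD is 0.13 to 0.40 in step 3.
- That the change contrast always costs precision. The variance ratio 2(1 − r)/(1 − r²) = 2/(1 + r) gives 43, 25 and 11% more variance at r = 0.4, 0.6 and 0.8, but only with no school effect. Sections 2.1 and 2.4 put one school in each arm, and step 5 shows the ordering reversing at a small school variance.
- That adjusting follow-up scores for baseline is always better. Step 4 shows that it leaves half of a stable school gap in place when r = 0.5, whereas the change contrast removes all of it.

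The exact equality also needs complete data. Section 2.9 expects otherwise ("Missing data will be handled by maximum-likelihood under MAR; if attrition exceeds 20%, multiple imputation will be used as a sensitivity analysis"), but the departures in step 1 are small and average out under random dropout.

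**Conclusion.** The point holds for the specification as written. With complete data the condition-by-time estimate is the unadjusted difference in change, with or without the covariate; with dropout this is nearly so. The claim of reduced bias from baseline differences fails for that contrast, and any narrower interval for it is not due to adjustment of the estimate. The mid- or end-season arm difference is adjusted, but with a slope that is too steep and a residual SD 15–17% too small for those rows. In step 4 it recovers the assumed effect under neither source of imbalance.

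The cancellation is algebraic and needs no assumed value. The slopes, SDs and effect sizes rest on equal variances, equal correlations and the assumed r; the size of any misreading scales with the baseline gap, which is unknown. The documents do not show which single-use specification is better, since that depends on whether the imbalance is a stable school difference or athlete-level chance.

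Severity is should-fix, not must-fix. Section 2.3 disclaims confirmatory inference, section 3 treats the quantitative results as exploratory, and condition stays confounded with school under any baseline model.

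**What to change.** Amend section 2.9 so that baseline is used once and the reported contrast is named before data are seen. Either:

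(a) make mid- and end-season the only response times, with baseline and baseline-by-time as covariates, and report the adjusted condition difference at each time; or

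(b) keep baseline as a response, drop the baseline covariate, and report the condition-by-time term plainly as a difference in change, without the claim of baseline adjustment.

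Report the other as a labelled sensitivity analysis. Say why both are shown: with one school per arm, a stable school difference can make (a) less precise and leave residual imbalance, while (a) is more precise if the imbalance is athlete-level chance.

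The cost is one or two sentences. Under (a), athletes with only a baseline survey add no rows, so their number should be reported by arm.
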